### The control group

The patients assigned to the control group will undergo curative surgery within two weeks after successful SEMS placement. After their recovery from surgery, they will receive adjuvant FOLFOX chemotherapy within four weeks. Adjuvant FOLFOX chemotherapy will be administered every two weeks for six months, totaling 12 cycles.

### The experimental group

The patients assigned to the experimental group will undergo neoadjuvant FOLFOX chemotherapy within two weeks after successful SEMS placement. After three cycles of neoadjuvant FOLFOX chemotherapy, the patient will undergo a follow-up study, including a serum CEA, abdomen and pelvic CT, and either a chest PA or chest CT, to determine the status of the tumor. If no metastatic lesions are found in these assessments, curative surgery will be performed within four weeks of the last administration of FOLFOX. After their recovery from surgery, they will receive adjuvant FOLFOX chemotherapy within four weeks. Adjuvant FOLFOX chemotherapy will be administered every two weeks for approximately four months, totaling nine cycles. The experimental group will receive a total of 12 cycles of perioperative FOLFOX chemotherapy. The flowchart of the study is presented in Fig. 1.

**Fig. 1 Fig1:**
[figure not shown]
The flowchart of the study on screening and treatment

### Chemotherapy

Two different regimens of oxaliplatin with 5-fluorouracil/leucovorin (FOLFOX) will be allowed in this study protocol. There are two types of chemotherapy regimens: FOLFOX-4 and mFOLFOX-6. FOLFOX-4 involves administering Oxaliplatin at a dose of 85 mg/m^2^ intravenously (IV) on the first day in 500 cc of 5% dextrose water over 2 hours, along with leucovorin at a dose of 400 mg/m^2^ IV or levoleucovorin at a dose of 200 mg/m^2^ IV. Additionally, 5-FU is administered at a dose of 400 mg/m^2^ as an intravenous bolus, followed by a continuous infusion of 600 mg/m^2^ for 22 h on the first and second days. The mFOLFOX-6 regimen involves administering Oxaliplatin at a dose of 85 mg/m^2^ IV on the first day in 500 cc of 5% dextrose water over 2 hours. Additionally, leucovorin is given at a dose of 400 mg/m^2^ IV or levoleucovorin at a dose of 200 mg/m^2^ IV. Additionally, 5-FU is administered at a dose of 400 mg/m^2^ IV bolus, followed by a continuous infusion of 2,400 mg/m^2^ IV over 46 h on the first and second days. The cycle will be repeated every two weeks in both regimens.

### Sample size and randomization

Based on our retrospective analysis, the 5-year overall survival (OS) rate for the control group was 84.1%. However, for patients who underwent curative surgery 4 weeks after SEMS placement without neoadjuvant chemotherapy, the OS rate was only 37.5%. The maximum response rate was assumed to be 80.0%, while the minimum response rate was assumed to be 40.0%. The non-inferiority limit for this study was set at 20%, which is half of 40%. Additionally, a non-inferiority margin of 60% was established. We determined the noninferiority margin for our study based on clinical judgment and retrospective data. We have chosen the noninferiority test as a method to minimize the unrealistic overall survival difference resulting from such a significant gap. We have set the non-inferiority limit for this study at 20%, which is relatively large. However, we believed that a 20% increase in OS with neoadjuvant therapy is possible and realistic, even though it is not a small number. Although it is generally advisable to choose a smaller value for the noninferiority margin, the feasibility of study recruitment was another important factor to consider. Therefore, we selected the noninferiority margin equivalent to a 20% increase in the expected OS rate. A non-inferiority log-rank test was conducted with a total sample size of 204 subjects, evenly divided between the control and experimental groups. The test achieved 80.1% power at a significance level of 0.050 to detect an equivalence hazard ratio of 2.29, assuming the actual hazard ratio is 1.00 and the hazard rate of the reference group is 0.0446. The study will last for six years, during which subject accrual (entry) will occur within the first three years. The accrual pattern is uniform across all time periods; all years are equal. The proportion of participants dropping out of the control group is 0.0100. The proportion of participants dropping out of the experimental group is 0.0100. The proportion of individuals switching from the control group to another group with a hazard rate equal to that of the experimental group is 0.0000. The proportion of individuals switching from the experimental group to another group with a hazard rate equal to that of the reference group is 0.0000. The estimated failure rate for stents is 8%. And, the failure rate for screening - indicating synchronous malignancies at other sites or patients requiring emergency operations - is 15%. A total of over 260 patients will be screened for the successful trial.

After the successful placement of self-expandable metal stents (SEMS), random allocation will be carried out with the consent of patients and their guardians. A total of 204 patients will be evenly distributed between the two groups in a 1:1 ratio. This study is a multicenter, randomized (1:1), parallel-group, open-label, controlled clinical trial. Using a random-number table, assignment codes will be concealed in opaque envelopes. To avoid the issue of tampering with the allocation from the sealed envelopes, the sealed opaque envelopes containing the randomization card, which is not visible through transillumination, are stored at the trial administration center (St. Vincent’s Hospital, Suwon, Korea). They are opened by a third party immediately after receiving a telephone call from the clinician who wishes to enroll a patient, in order to minimize the risk of allocation manipulation. The sealed envelopes will be used but will be open by a centralized system. Half of the patients will be randomly assigned to the control group, while the other half will be assigned to the experimental group through randomization.

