### Endpoint

The primary endpoint will be the 3-year OS rate after curative surgery. The time of SEMS placement will serve as the origin for survival analysis in both groups, ensuring a consistent starting point. The rates of complications related to SEMS, postoperative complications within 30 days after surgery, chemotherapy-related adverse events, stoma formation, stoma-free survival, recurrence, 3-year disease-free survival (DFS), and QoL will be analyzed as secondary outcomes. Circulating tumor DNA (ctDNA) will be collected at specific time points, including after SEMS placement, before and after curative resection, after neoadjuvant chemotherapy, and after every three cycles of chemotherapy. Through the analysis of serial samples of ctDNA, our objective is to determine the correlation between treatment strategies and oncologic outcomes. This will provide a basis for individualizing treatment in patients with obstructive colon cancer.

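### The primary endpoint is named as the 3-year OS rate, but the margin, power and Cox rule concern survival over all follow-up, and the 20-point limit is a 5-year figure (13.9 points at 3 years)

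*Protocol article*

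**What the plan says.** Three sections of the protocol article bear on this.

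- **Endpoint:** "The primary endpoint will be the 3-year OS rate after curative surgery".
- **Sample size and randomization:** planning starts from retrospective data in which "the 5-year overall survival (OS) rate for the control group was 84.1" per cent. It then assumes rates of 80% and 40%, takes half of that 40-point gap as a 20-point limit, and adds: "Additionally, a non-inferiority margin of 60% was established". No time point is attached to the 80%, the 60% or the 20 points. The power statement reads: "The test achieved 80.1% power at a significance level of 0.050 to detect an equivalence hazard ratio of 2.29". Behind it stand a true ratio of 1.00 and a control-arm hazard of 0.0446. The other inputs are 204 patients split 1:1, three years of uniform accrual in a six-year study, and 0.0100 dropout in each arm.
- **Statistical analysis:** non-inferiority on the primary endpoint is judged by an unadjusted Cox model. The upper one-sided 95% limit of the hazard ratio must lie below 2.29 in both the ITT and the PP population. No cut at 3 years is stated.

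**The concern.** The named endpoint is a survival probability at one time. The margin, the event count and the test belong to a hazard ratio over follow-up of three to six years per patient. No section connects the two. Three things are at stake.

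- **The tolerated loss.** Someone who combines the 20% limit with the 3-year endpoint will take the trial to accept a 20-point loss at 3 years. The hazard-ratio rule does not implement that.
- **The primary analysis.** The text leaves open whether deaths after 3 years count. That choice should be fixed before the data are seen, because it changes the number of deaths and the power.
- **The interpretation.** A 3-year rate and a hazard ratio carry the same information only under proportional hazards. One arm has surgery within two weeks of stenting and the other has three chemotherapy cycles first, and the protocol itself plans for non-proportionality. The two measures could then disagree, and the document does not say clearly which decides.

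**Working it through.** **Inputs, all from the sample-size section:** rates 80% and 60%; hazard h = 0.0446, read as per year; margin HR 2.29; true HR 1.00; N = 204; accrual 3 years; study length 6 years; dropout 0.0100, read as 1% per year, so d = -ln(0.99) = 0.01005. The one-sided 5% level follows the one-sided 95% limit in the analysis section.

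**1. Where the margin and hazard come from**
- ln(0.60)/ln(0.80) = 2.289, the stated 2.29. This ratio is the same whatever time the 80% and 60% refer to, so it does not fix the time point.
- -ln(0.80)/5 = 0.0446, the stated hazard. If 80% were a 3-year rate, the hazard would be -ln(0.80)/3 = 0.0744. The hazard therefore places the 80% and 60%, and with them the 20-point limit, at 5 years.

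**2. The stated power**
- h + d = 0.05465. With follow-up uniform between 3 and 6 years, P(death) = (h/(h+d)) × [1 - (e^(-3(h+d)) - e^(-6(h+d)))/(3(h+d))] = 0.816 × [1 - (0.8488 - 0.7204)/0.1640] = 0.177.
- Expected deaths: 204 × 0.177 = 36.15.
- Power = Φ(ln 2.29 × √36.15/2 - 1.645) = Φ(0.846) = 80.1%. This is the protocol's figure, and it counts deaths after 3 years.
- Variants: 80.9% without dropout, 79.0% (35.0 deaths) if follow-up stops at 5 years, 70.2% with a two-sided 5% level. A simulated Cox test with all follow-up (8,000 trials) gave 78.7%.

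**3. What HR 2.29 means at 3 years**
- Control: e^(-3 × 0.0446) = 87.5%.
- At the margin: 0.8748^2.29 = 73.6%.
- Difference: 13.9 points.
- A 20-point loss at 3 years would be ln(0.6748)/ln(0.8748) = HR 2.94.

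**4. If the Cox comparison were cut at 3 years per patient**
- P(death) = 0.816 × (1 - 0.8488) = 0.1234, giving 25.2 deaths.
- Power = Φ(ln 2.29 × √25.2/2 - 1.645) = Φ(0.434) = 66.8% (67.3% without dropout; 65.7% in simulation).
- Keeping 80.1% under that cut needs 36.13 deaths, or 36.13/0.1234 = about 293 patients.

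**5. If 3-year rates were compared directly against 13.9 points**
- SE = √(2 × 0.8748 × 0.1252/102) = 0.0463.
- Power = Φ(0.1387/0.0463 - 1.645) = about 91% with complete follow-up. A simulated Kaplan-Meier comparison with dropout gave about 90%. The protocol does not specify this test.

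**The case against.** The strongest reply is that nothing in the calculation fails. The hazard, the margin and the power all reproduce. The analysis section sets no 3-year cut, the study runs six years, and visits are scheduled up to five years. On those terms the test has its stated power. This stands in full.

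It also rules out three stronger readings that a reader might infer:

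- **The trial has only 67% power.** That figure requires censoring every patient at 3 years, a rule the document does not state. It is the consequence of one possible reading, not a property of the test as written.
- **Any 3-year analysis would fall short of the stated power.** Step 5 shows otherwise: a direct comparison of 3-year rates against 13.9 points would have about 90% power with the same 204 patients.
- **The protocol declares a 20-point margin for 3-year OS.** It does not. It gives 20% with no time point, and the hazard shows that it belongs to 5 years. At 3 years the hazard-ratio rule tolerates less than 20 points under the planning model, so the mismatch does not loosen the test.

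It can also be said that under proportional hazards the hazard ratio and the 3-year rate are interchangeable. They are, but only after a conversion that the document never makes. The reply therefore leaves the mismatch between the named endpoint and the planned test unanswered.

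**Conclusion.** The endpoint definition does not match the basis of the sample size or the decision rule. The planned test has about 80% power, but for overall survival over all follow-up, whereas the endpoint named as primary is the 3-year OS rate. The 20-point limit is a 5-year quantity. Its 3-year counterpart is 13.9 points (87.5% against 73.6%). Power of about 67% on about 25 deaths applies only if the Cox analysis is cut at 3 years.

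These figures assume exponential survival at 0.0446 per year, proportional hazards, uniform accrual and 1% yearly dropout. That the 80% and 60% are 5-year rates is inferred from the hazard; the text labels only the 84.1% as 5-year. Dropout hardly matters: ignoring it moves power by less than one point. Because the primary endpoint, the margin and the decision rule are all involved, the text should be reconciled before analysis.

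**What to change.** Name the primary endpoint as overall survival over all follow-up to the six-year cut-off, from the time origin the Endpoint section already sets. Test it by the existing rule (upper one-sided 95% limit of the hazard ratio below 2.29), and report the 3-year OS rate descriptively. In the sample-size section, state that 2.29 corresponds to 80% against 60% at 5 years and to 87.5% against 73.6% at 3 years under exponential survival. The 80.1% power and the 204 patients then stand. The cost is a wording change in the protocol and in any analysis plan, with no extra patients.

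If the sponsor instead wants a Cox test limited to 3 years, that cut should be written into the analysis section and the power restated as about 67%. Holding 80.1% under that rule would take about 293 patients.

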### Follow-up

Follow-up data will be obtained for all patients during routine clinical practice. During each follow-up office visit, patients will undergo evaluation using CEA, abdomen and pelvic CT, and either chest PA or chest CT. Annual colonoscopic surveillance will be performed. Patients will undergo examinations every three months for the first two years, and then every six months for the remaining three to five years of the schedule.

### Endpoint

The primary endpoint will be the 3-year OS rate after curative surgery. The time of SEMS placement will serve as the origin for survival analysis in both groups, ensuring a consistent starting point. The rates of complications related to SEMS, postoperative complications within 30 days after surgery, chemotherapy-related adverse events, stoma formation, stoma-free survival, recurrence, 3-year disease-free survival (DFS), and QoL will be analyzed as secondary outcomes. Circulating tumor DNA (ctDNA) will be collected at specific time points, including after SEMS placement, before and after curative resection, after neoadjuvant chemotherapy, and after every three cycles of chemotherapy. Through the analysis of serial samples of ctDNA, our objective is to determine the correlation between treatment strategies and oncologic outcomes. This will provide a basis for individualizing treatment in patients with obstructive colon cancer.

### Circulating tumor DNA analysis

Peripheral venous blood samples will be collected from patients at the aforementioned time points. At least 20 mL of blood will be collected in tubes containing EDTA. The plasma was separated within four hours of sample collection. The plasma obtained will undergo centrifugation at 2000 g for 5 min and at 16,000 g for 10 min. It will then be immediately aliquoted and stored at -80 °C. To isolate cell-free DNA from 4 mL of plasma, we will use a MagMAX Cell-Free DNA Isolation Kit (Applied Biosystems, Foster City, CA, USA) along with a KingFisher Duo Prime Magnetic Particle Processor (Thermo Fisher Scientific, Waltham, MA, USA), following the instructions provided by each manufacturer. The concentration of purified plasma cell-free DNA was measured using a Qubit 2.0 fluorometer (Thermo Fisher Scientific, Waltham, MA, USA) in conjunction with a Qubit dsDNA HS Assay Kit (Thermo Fisher Scientific, Waltham, MA, USA), following the manufacturer’s instructions.

The sequence data will undergo primary and secondary analyses using the standard Ion Torrent Suite Software, which will be operated on a Torrent Server. The raw signal data will be analyzed using Torrent Suite v5.10.1 and Ion Reporter software (Thermo Fisher Scientific, Waltham, MA, USA). The pipeline will include several steps, such as signal processing, base calling, quality score assignment, adapter trimming, PCR duplicate removal, read alignment, quality control of mapping quality, coverage analysis, and variant calling. The sequencing reads will be aligned to the UCSC hg19 reference genome (Genome Reference Consortium GRCh37). Sequence variants will be identified using the Ion Reporter software v5.10 and the Ion AmpliSeq HD Workflow template for Liquid Biopsy - w1.4 - DNA - Single Sample (Thermo Fisher Scientific, Waltham, MA, USA). The coverage of each amplicon will be determined using the Coverage Analysis Plugin software version 5.10.0 (Thermo Fisher Scientific, Waltham, MA, USA). The use of UMIs will enable the categorization of reads into molecular families. Random errors generated during the library construction and sequencing process will be automatically removed.

### Statisticl analysis

The analysis will be conducted following the intention-to-treat (ITT) principle, meaning that patients will be evaluated based on their assigned treatment, regardless of whether they completed the adjuvant chemotherapy. Additionally, a per-protocol (PP) analysis will be performed, which will consider the treatment that was actually administered, except in cases of significant deviations, such as early dropout before follow-up evaluations or during treatment. The primary analysis will encompass both ITT and PP populations. For the non-inferiority assessment of the primary endpoint, a one-sided 95% confidence interval (CI) will be calculated using the unadjusted Cox proportional hazards model. Non-inferiority will be declared if the upper limit of this one-sided 95% CI of the hazard ratio (HR) is less than 2.29 (the pre-specified non-inferiority margin) in both the PP and ITT analyses. The proportionality assumption will be assessed using both log-negative-log plots and Schoenfeld residuals. If it is determined that the assumption of proportional hazards has been violated, a landmark analysis will be performed by defining a clinically meaningful time point. Comparisons between continuous variables will be conducted using the Wilcoxon rank-sum test or the two-sample t-test, depending on the data’s normality. Categorical variables will be analyzed using the chi-square test. Survival probability analysis will be conducted using the Kaplan-Meier method. The log-rank test will be used to assess the difference in survival rates between groups. Significance will be defined as a p-value of 0.05 or lower. All statistical analyses will be performed using version 23.0 of the Statistical Package for the Social Sciences (SPSS) for Windows (SPSS, Inc., Chicago, IL).

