## Methods and design

### Patient enrollment

This study was designed as a multicenter, prospective, non-inferiority, randomized, controlled comparative study. The study will last approximately six years, consisting of three years of inclusion and three years of follow-up. Patients will be enrolled at eight University hospitals affiliated with The Catholic University of Korea, including Seoul St. Mary’s Hospital, Yeouido St. Mary’s Hospital, Uijeongbu St. Mary’s Hospital, St. Vincent’s Hospital, Incheon St. Mary’s Hospital, Eunpyeong St. Mary’s Hospital, Bucheon St. Mary’s Hospital, and Daejeon St. Mary’s Hospital. Complete information will be provided to patients and their guardians after the successful placement of SEMS for obstructive lesions on the left side of the colon. Informed consent will be obtained from the patients after pathologic confirmation of adenocarcinoma and completion of preoperative staging work-up.

Consecutive adult patients between the ages of 20 and 75 with pathologically confirmed adenocarcinoma will be eligible if they meet the following criteria: clinical stage II or III colon cancer with colonic obstruction; a colon cancer located between the splenic flexure colon and rectosigmoid junction colon, defined as a tumor located above 15 cm from the anal verge; no colonic injury and successful decompression of the colon within 48 h after SEMS placement; Eastern Cooperative Oncology Group (ECOG) performance status of 0–2; American Society of Anesthesiologists (ASA) physical status grade I, II, or III; and a negative urine human chorionic gonadotropin (hCG) test in women who are in their fertile period.

Patients will be excluded from the study if there is any suspicion of distant metastasis or the presence of another primary malignant lesion. Additionally, patients with a clinical stage of T1 or T2 and N0 will be excluded if they exhibit signs of perforation or severe ischemia that necessitates emergency surgery. Other exclusion criteria include complications related to the placement of self-expanding metal stents (SEMS), such as infection, severe bleeding, or perforation following SEMS placement, as well as colonic obstruction caused by benign strictures.

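### The primary non-inferiority model is fixed as unadjusted although clinical stage is known before randomisation; adjusting for stage is a cheap, minor improvement

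*Protocol article*

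**What the plan says.** The statistical analysis section of the protocol article specifies the decisive model: "a one-sided 95% confidence interval (CI) will be calculated using the unadjusted Cox proportional hazards model". The rule follows at once: "Non-inferiority will be declared if the upper limit of this one-sided 95% CI of the hazard ratio (HR) is less than 2.29", and it must be met in both the PP and the ITT analysis. No stage-adjusted or stage-stratified analysis of the primary endpoint is described.

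The patient enrollment section admits patients with "clinical stage II or III colon cancer with colonic obstruction". It takes consent only after the staging work-up, so stage is on record before allocation.

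On allocation, the sample size and randomization section says: "Using a random-number table, assignment codes will be concealed in opaque envelopes". It names no stratification factor. The same section sets the trial at 204 patients, 102 per arm, with a margin of 2.29, a true hazard ratio taken as 1.00 and a control hazard of 0.0446. On power it says: "The test achieved 80.1% power at a significance level of 0.050".

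**The concern.** With few deaths, the estimated hazard ratio is imprecise and the pass mark is close to 1. Stage is a plausible strong predictor of death. If the arms differ by chance in their share of stage III patients, an unadjusted hazard ratio carries that difference into the verdict, while a stage-adjusted one largely removes it. The information is already collected and costs nothing to use.

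The PP analysis adds a second reason. Randomisation protects the ITT comparison, but PP drops patients for events after randomisation. In the experimental arm surgery depends on restaging after chemotherapy, a step the control arm does not have. PP exclusions could therefore differ by arm and by stage, and nothing in an unadjusted PP model corrects for that.

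**Working it through.** **Inputs from the document.** 204 patients, 102 per arm; control hazard 0.0446 per year; uniform accrual over 3 years, 6 years in total; dropout 0.01 per arm (read as annual); margin 2.29; one-sided 95% limit.

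**Assumptions not in the document.** 50% of patients are stage III; stage III versus II hazard ratio for death of 1.5, 2 or 3; exponential survival; allocation not stratified by stage.

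**1. The plan's own figures.**
- Control hazard: −ln(0.80)/5 = 0.0446. Margin: ln(0.60)/ln(0.80) = 2.289. Both match.
- Let s = 0.0446 + 0.01005 = 0.0547 (death plus dropout hazard). Chance of an observed death = (0.0446/s) × [1 − (e^(−3s) − e^(−6s))/(3s)] = 0.816 × 0.217 = 0.177. Times 204, this gives about 36.2 deaths at HR 1.
- Power = Φ(ln 2.29 × √36.2/2 − 1.645) = Φ(0.847) = 80.1%. The stated power reproduces with one-sided 0.05; two-sided 0.05 would give about 70%.

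**2. The pass mark.** SE of log HR = 2/√36.2 = 0.33. The largest observed HR that passes is exp(ln 2.29 − 1.645 × 0.3324) = about 1.325.

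**3. How far stage imbalance moves the unadjusted HR.** The SD of the difference in stage III share is √(2 × 0.25/102) = 7.0 points, so 1.96 SD is about 13.7 points. The shift is roughly [1 + a(h − 1)]/[1 + b(h − 1)], with a and b the stage III shares (0.569 and 0.431) and h the stage HR:
- h = 1.5: 1.284/1.216 = 1.06
- h = 2: 1.569/1.431 = 1.10
- h = 3: 2.137/1.863 = 1.15

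A shift of 1.10 changes the verdict only if the observed HR is already near the pass mark, roughly 1.20 to 1.32.

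**4. How often the imbalance occurs.** A difference of 10 or more patients (9.8 points) in one direction has probability of about 1 − Φ((9.5/102)/0.070) = 1 − Φ(1.33) = 9%. Not counting a difference of exactly 10, it is 1 − Φ((10.5/102)/0.070) = 1 − Φ(1.47) = 7%.

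**5. Simulation of the rule.** 120,000 trials per scenario with the inputs above; Cox with and without stage; upper limit compared with 2.29. The null is 80% versus 60% five-year survival, the protocol's own basis for the margin. Each cell shows unadjusted / adjusted.

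| | Stage HR 1.5 | Stage HR 2 | Stage HR 3 |
|---|---|---|---|
| False non-inferiority, all trials | 5.2% / 4.9% | 5.1% / 4.6% | 5.0% / 3.8% |
| False non-inferiority, imbalance favours experimental arm | 7.2% / 4.8% | 8.8% / 4.7% | 11.3% / 3.8% |
| Power at HR 1, all trials | 79.0% / 78.8% | 79.0% / 78.7% | 79.1% / 78.8% |
| Power at HR 1, imbalance against experimental arm | 75.6% / 79.1% | 71.2% / 77.6% | 67.4% / 77.8% |
| Different verdicts at HR 1 | 2.2% | 3.3% | 4.9% |

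The imbalance rows use differences of 10 or more patients (about 11,000 trials each; Monte Carlo SE at most about 0.4 points). Smaller runs of the same model gave 3% to 4% for adjusted error in the favourable tail. In the opposite tail they gave up to 79% power unadjusted and 79% to 81% adjusted. Gaps of that size are sampling noise: with 3,000 trials a 9% tail holds about 270, and the SE at 75% power is √(0.75 × 0.25/270) = 2.6 points.

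**6. Scale of the margin.** 60% against 80% marginal survival corresponds to a within-stage HR of 2.30, 2.33 and 2.39 for stage HR 1.5, 2 and 3.

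**The case against.** The strongest case against is that nothing here is an error. An unadjusted Cox model in a randomised ITT comparison is valid; its interval already allows for chance imbalance, and it matches the log-rank test used for the sample size. The margin was built from marginal survival, so the unadjusted hazard ratio is on the margin's own scale. The stage mix and stage effect are assumptions, and at a stage HR of 1.5 the gain is small. All of this stands.

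Two stronger readings are tempting, and the document supports neither.

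- **That the rule runs at two to three times its nominal 5% error.** Figures of 10.5% to 14.8% arise only in the roughly 7% of trials with a clear imbalance towards the experimental arm, for stage HRs of 2 to 3, and when 2.29 is read as a within-stage hazard ratio. Part of that excess is scale mismatch: on that reading the unadjusted rule already shows 6.4% to 6.5% with no selection on imbalance. On the protocol's own null the tail figure is 7% to 11%, and the opposite tail offsets it, so overall error stays at about 5%.
- **That randomisation is unstratified.** The article names no factor, but a condensed article may leave this to the full protocol. If allocation is stratified by stage, disagreement between the models at HR 1 falls to 0.7% to 1.7%.

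The scale objection does not defeat the change. The conditional equivalent of the margin is 2.30 to 2.39, so keeping 2.29 errs slightly on the strict side. Nor does the validity argument fully cover PP, because exclusions after randomisation are not protected by it. Since ITT must pass too, the consequence is a weaker PP safeguard rather than a higher ITT error. Stage adjustment would remove only the stage-related part of any PP selection.

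**Conclusion.** Minor: an analysis choice that can be improved, not an invalid one. The unadjusted ITT rule has about 79% simulated power and about 5% error averaged over trials. Stage adjustment with 2.29 kept gives practically the same average power, slightly lower average error (about 4% to 5%), and protection in the trials where stage happens to be imbalanced. The two models disagree in about 2% to 5% of trials at HR 1, in both directions and only for borderline results. The sizes depend on the assumed 50% stage III share and stage HR of 1.5 to 3. The premises that the model is fixed as unadjusted and that stage is known beforehand come directly from the document.

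**What to change.** Before outcome data are seen, replace the unadjusted Cox model in the statistical analysis section with a Cox model adjusted for, or stratified by, clinical stage at enrolment (II versus III). Apply it in both ITT and PP, keep the limit of 2.29, and report the unadjusted hazard ratio as a sensitivity analysis.

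The cost is one sentence. It needs no new data and no more patients, and the software already named can fit the model. The downside is that the hazard ratio becomes stage-conditional. The plan should say so, and should say that keeping 2.29 is slightly stricter than the marginal margin it came from.
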